**Effects of exercise on disease activity and cardiovascular risk factors in patients with ankylosing spondylitis**

**SUMMARY**

**Background:** Exercise is recommended as a cornerstone in the treatment of ankylosing spondylitis (AS) together with medication. Last years, increased risk of cardiovascular diseases in patient with inflammatory diseases is reported, probably caused by inflammation and increased prevalence of traditional risk factors. In both healthy adults and other patient groups, cardiorespiratory and muscular strength exercises have been shown to have a positive effect on inflammation as well as on cardiovascular risk factors. To our knowledge this has not been shown in patients with AS.

**Objective:** The aim of this study is twofold: firstly, to investigate the effects of a supervised exercise program on disease activity and cardiovascular risk factors in patients with AS, and secondly, to examine acute effects on physiological responses to exercise.

**Design:** Single blind randomized controlled trail.

**Participants:** Patients who were classified with high disease activity in a cross sectional study carried out between 2008 and 2010 will be invited to participate (REK nr: s-03066 and S-02059). In addition, patients will be recruited from the rheumatologic outpatient clinic at Diakonhjemmet Hospital.

**Intervention:**  Supervised cardiorespiratory and muscular strength exercise program, one hour three times a week for twelve weeks.

**Primary outcome:** Disease activity (inflammatory markers and patient reported)

**Secondary outcomes:** Physical fitness, body composition, waist circumference, depression, physical activity level, arterial stiffness, endothelial function. Blood samples analyzed for both markers of disease activity and cardiovascular risk. Acute exercise responses: heart rate, respiration, oxygen uptake, plasma concentrations of lactate, interleukin-6, interleukin-18, tnf-alpha.

Contents

[Background 4](#__RefHeading___Toc295835609)

[Inflammatory markers 4](#__RefHeading___Toc295835610)

[Markers of cardiovascular disease and vascular function 4](#__RefHeading___Toc295835611)

[Exercise in patients with ankylosing spondylitis 5](#__RefHeading___Toc295835612)

[Acute responses to exercise in patients with ankylosing spondylitis 6](#__RefHeading___Toc295835613)

[Objective 6](#__RefHeading___Toc295835614)

[Methods 6](#__RefHeading___Toc295835615)

[Design 6](#__RefHeading___Toc295835616)

# Background

Ankylosing spondylitis (AS) is an inflammatory rheumatic disease affecting mainly the axial skeleton and sacroiliac joints presenting around 20-30 years of age (1). The overall prevalence is between 0.1 % and 1.4 % and higher among men than women, with a ratio of roughly 2 to 1 (1). Typical disease characteristics are inflammatory back pain, which may lead to structural and functional impairments, but AS may vary considerably with regard to disease symptoms and severity (2;3). Recently there has been an increased focus on the high risk of cardiovascular diseases (CVD) among patients with AS compared to the general population. The mortality rate among patients with AS is reported to be 1.7-1.9 higher than the general population, and the main reason for the increased mortality rate is cardiovascular events (4). The reason for the increased risk of cardiovascular diseases in patients with AS is still unclear. However, it is thought to be due to the inflammatory burden and an increased prevalence of traditional risk factors (5), which are factors that have an important role in accelerating atherosclerosis (6;7). There is a need for more research to explore the underlying mechanisms for the increased risk of CVD. In addition, interventions aiming at prevention of CVD should be investigated.

### Inflammatory markers in patients with AS

The exact level of inflammatory markers in patients with AS is not established, but studies have reported increased levels of C-reactive protein, sedimentation rate, tnf-alpha, interleukin 6, interleukin 18 (8-10). The recently launched AS disease activity score (ASDAS) is shown to reflect level of inflammation (11). This indicates that ASDAS can be used as an indirect measure of inflammatory status in patients with AS.

### Markers of cardiovascular disease and vascular function

There are several surrogate markers of vascular functions and atherosclerosis. Pulse wave velocity (PWV) analysis is a non-invasive way of assessing arterial stiffness, and a surrogate marker of vascular function. Increased arterial stiffness has been shown to correlate with coronary atherosclerosis and to predict coronary events and mortality in patients with hypertension (12). PWV is the gold standard of arterial stiffness measurements and has been reported to be reduced during anti-inflammatory treatment (13). Peripheral artery tonometry is another surrogate marker of cardiodiovascular disease and reflects endothelial function. It has been found to correlate strongly with coronary endothelial function and future cardiovascular events (14). In addition, reduced endothelial function is on of the first markers on atherosclerosis. The gold standard for measuring endothelial function is the flow mediated dilatation (FMD)-method and a reduction in FMD is often used as a early marker for arteriosclerosis (15). Studies have also showed that the developement og atherosklerosis include a chronich inflammatory prosess in the vascular wall and increased levels of vascular cell adhsions molecules (E-selectin, P-selectin and, ICAM-1 and VCAM-1) (16-18).

### Exercise as part of the disease management

Exercise is recommended as a cornerstone in the treatment of AS (19). A systematic review of exercise trials in patients with AS concluded that exercise has a beneficial effect on pain, spinal mobility, physical function and patient global assessment (20). The interventions in these trials focused mainly on flexibility training, and the effects on inflammatory markers and cardiovascular risk factors were not measured in any of the studies. However, in healthy adults’ cardiorespiratory exercise and muscular strength exercises are recommended for prevention of cardiovascular diseases (21). In line with this, intervention studies have shown that exercise have favorably effects on inflammation markers (22-24) and risk factors for cardiovascular diseases such as triglycerides(25), HDL-cholesterol(25), blood pressure(26), central obesity (27;28) and glucose tolerance(29) in healthy adults and other patients groups. Despite this, there is limited evidence on the effects of exercise on inflammation and traditional CV risk factors in patients with inflammatory rheumatic diseases. Intervention trials have shown that exercise has a favorable effect on body composition (30) and sedimentation rate (31) in patients with rheumatoid arthritis. Also in an observational study, Metsios et al. (32) found that physically inactive RA patients had a significantly higher systolic blood pressure, elevated total cholesterol and higher low-density lipoprotein cholesterol than physically active RA patients.

In line with this, in a recent cross sectional study, we found that cardiorespiratory fitness was inversely associated with disease activity in patients with AS. Furthermore, we found that high levels of cardiorespiratory fitness was significantly associated with lower risk of having metabolic syndrome, lower body mass index, smaller waist circumference, lower triglycerides and lower systemic inflammation in patients with AS and population controls (without rheumatic diseases). However, an important difference between population controls and patients was observed: high cardiorespiratory fitness was associated with lower blood pressure and higher levels of HDL-cholesterol in the controls, whereas these associations were absent in the patient group. Accordingly, there is a need to investigate the effects of exercise on inflammatory markers and cardiovascular risk factors in patients with AS.

### Acute responses to exercise in patients with AS

Even though exercise is recommended as part of the treatment, there is limited data on the acute physiological responses to exercise in AS patients. Carbon et al. examined responses to 30 min of cycling (33), and showed increased levels of neutrophils, leukocytes and lymphocytes which normalized quickly after exercise. The responses were similar to that seen in healthy controls. Interestingly, they also showed a small improvement in spinal flexibility immediately after exercise which normalized over the subsequent 3-5 hours. Exercise did also induce a marked increase in white blood cells, but there were no association between changes in the different variables. We have not been able to find any papers on how cytokines change with acute exercise. Of particular interest are the responses in inflammatory parameters such as interleukin-6, interleukin-18 and tnf-alpha. In addition, we want to examine cardiovascular and metabolic responses. Due to the underlying inflammation of AS patients, one might expect that they respond differently during an exercise bout. In addition, it will be of interest to investigate to what extent these responses are altered during long-term exercise.

# Objective

The aim of this study was twofold: firstly to investigate the effects of a supervised cardiorespiratory and muscle strengthening exercise program on disease activity and cardiovascular risk factors in patients with AS, and secondly, to examine acute effects on physiological responses to exercise.

# Methods

### Design

This study will be designed as a single blind randomized controlled trial.

### Participants

Patients who were classified with high disease activity in a cross sectional study carried out between 2008 and 2010 will be invited to participate (REK nr: s-03066 and S-02059). In addition, patients will be recruited from the rheumatologic outpatient clinic at Diakonhjemmet Hospital.

##### Inclusion criteria:

- Diagnosis of AS, confirmed by a rheumatologist
- Age, 18-70 -years.
- Not using TNF-α medication or steady medication for ≥3 months
- Disease activity ≥2.1 on ASDAS score defined as high disease activity (corresponding to a BASDAI score of ≥3.5).
- Not participated in a structured cardiorespiratory or muscle strengthening exercise program during the last year, including large amounts of brisk walking.

##### Exclusion criteria:

- Known cardiovascular disease.
- Severe comorbidity which involves reduced exercise capacity
- Not able to participate in weekly exercises sessions in Oslo.

### Sample size

To estimate the sample size we used the defined minimal clinical important difference in ASDAS score, which is 1.1 points (34). Based on a cross-sectional study recently carried out at our clinic we estimated the standard deviation to be 1.0. Power was set at 80% and α-value was set at 0.05 and drop-out rate was set at 20%. Based on these assumptions we estimated a sample size of 17 participants for each group. To ensure sufficient power also for secondary outcomes, a total of 40 participants are needed for this study.

### Randomization

A person, not involved in other aspects of the study, will assign the participants to either the exercise group (EG) or the control group (CG) following a computerised randomization program. A block randomization procedure will be used.

### Assessments

All assessments will be conducted at Diakonhjemmet Hospital. An independent assessor, unaware of the assignment to EG or CG, will examine the participants performed before randomization and after the intervention period.

### Outcome measures

##### Primary outcome: Disease activity

The AS Disease Activity Score-C-reactive protein (ASDAS-CRP) will be used to assess disease activity. ASDAS is reported to be associated with inflammatory biomarkers (11). The ASDAS is reported to have high face validity as it was developed through a Delphi process of experts and patients. It is a continuous measure based on patient-reported outcomes (back pain, duration of morning stiffness, patient global assessment and peripheral join complaints) and CRP, and higher values indicate higher disease activity. The minimal clinically important improvement for this instrument is reported to be ∆ ≥1.1, and ∆ ≥2.0 is considered a major improvement(34).

##### Secondary outcome measures

**Electrocardiography:** to measure the electrical activity of the heart.

**Blood samples:** Analyzed for both general and endothelial specific markers of inflammation and cardiovascular risk (NTproBNP, OPG, RANKL, VEGF, adhesion molecules, TNF-α, IL-6, IL-18, troponin T, high sensitive C-reactive protein, sedimentation rate, total cholesterol, LDL-cholesterol, HDL-cholesterol, triglycerides, apolipoprotein B, apolipoprotein A1, Lipoprotein A).

**Arterial stiffness and endothelial function:**  Measured using the Sphygmocor and Itamar respectively. In addition, the FMD-method will be used to measure endothelial function. Before examination of arterial stiffness at least four hours should have passed from the last meal, cigarette or cup of coffee. 10 hours should have passed from the last intake of alcohol.

**Blood pressure:** Resting diastolic-, systolic and mean arterial blood pressure will be measured.

**Cardiovascular health status:** The patients will be asked to complete a questionnaire reporting on the presence of CVD, the use of medication, smoking, and family history related to the incidence of CVD.

**Physical fitness:** Cardiorespiratory fitness will be assessed with an indirect maximal walking test on a treadmill for estimation of peak oxygen uptake according to modified Balke protocol. Hand grip strength will be assessed with GRIPPIT. Spinal and hip mobility will be assessed with the Bath Ankylosing Spondylitis Metrology index (BASMI), and chest expansion will be measured as the difference between maximal inspiration and expiration at the level of xipoideus (cm).

**Acute physiological responses to exercise:** Will be assessed with a submaximal exercise test (at a fixed work load) and as a part of the maximal treadmill test. The submaximal constant load test will be an integrated part of the warm-up procedure before the maximal treadmill test. Before and immediately after the submaxmial and the maximal bouts, blood samples will be taken. Additional samples will be taken during the maximal test and 5 min post exercise. The blood samples will be analyzed to determine the concentration of  interleukin 6 and 18, tnf-alpha and lactate. Heart rate will be recorded continually during and after the exercise bouts.

**Body composition:** Weight, height, waist circumference will be measured. Dual Energy X-ray Absortiometry (DEXA) will be used to assess body composition.

**Physical function:** Will be assessed with the patient reported index Bath Ankylosing Spondylitis Functional Index (BASFI).

**General health:** Will be assessed with the generic General Health Questionnaire (GHQ-12).

**Physical activity level:** Will be assessed with the International Physical Activity Questionnaire short version (IPAQ-s).

###

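### Acute IL-6, IL-18 and TNF-alpha are measured as plasma concentrations without haemoglobin or haematocrit, so a small within-person rise around the maximal bout cannot be told apart from plasma-volume loss

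*Protocol*

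**What the plan says.** The Objective section makes acute responses the second of two study aims: "secondly, to examine acute effects on physiological responses to exercise". The Summary lists the outcomes under this aim: "Acute exercise responses: heart rate, respiration, oxygen uptake, plasma concentrations of lactate, interleukin-6, interleukin-18, tnf-alpha".

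The paragraph on acute physiological responses, under Secondary outcome measures, sets two bouts: a submaximal test at a fixed load, used as warm-up, followed by the maximal treadmill test. On sampling it says "Before and immediately after the submaxmial and the maximal bouts, blood samples will be taken" and "Additional samples will be taken during the maximal test and 5 min post exercise". On the laboratory work it says "The blood samples will be analyzed to determine the concentration of interleukin 6 and 18, tnf-alpha and lactate".

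The background section on acute responses shows how the results will be read: "Of particular interest are the responses in inflammatory parameters such as interleukin-6, interleukin-18 and tnf-alpha". It adds a longer-term question: "it will be of interest to investigate to what extent these responses are altered during long-term exercise".

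Neither the acute analyte list nor the general blood-sample list includes haemoglobin, haematocrit or total protein. Plasma volume is not mentioned. No sample later than 5 min after exercise is listed, and no sampling session without exercise is described.

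**The concern.** A plasma concentration is an amount divided by a volume. Hard exercise can move water out of the plasma for a short time. A protein retained in the circulation then becomes more concentrated although none has been released. The sampling times fall where such a shift would be present: during the maximal test, at its end, and 5 min later. With no later sample, the data also cannot show whether a rise fades as fluid returns.

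The second aim is at stake. The Protocol wants to read changes in IL-6, IL-18 and TNF-alpha as inflammatory responses, and says that it found no papers on how cytokines change with acute exercise. It therefore has no basis for expecting true changes so large that a shift of several per cent would not matter. If a true change is small or absent, much or all of the observed rise could be concentration alone.

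This is a gap in data collection. The choice of formula can be left to an SAP, but the measurements that the formula needs must be taken at the time of the test.

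**Working it through.** The Protocol gives no figure on this point to reproduce. Its one calculated figure, 17 per group for ASDAS, does not enter.

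**Inputs from the Protocol:** the four analytes and the sampling times (Secondary outcome measures); 40 participants and 20% drop-out (Sample size); assessments before randomisation and after the intervention (Assessments).

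**Inputs assumed, because the Protocol gives none:** the fractional plasma-volume loss f, the standard deviation (SD) of the within-person log change, and the true fold change of a marker. Each is shown as a range.

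**Step 1. Rise with no release.** If the amount is constant and volume falls by the fraction f, the rise is 1/(1 − f) − 1.

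| Assumed f | Calculation | Apparent rise |
|---|---|---|
| 5% | 1/0.95 − 1 | 5.3% |
| 10% | 1/0.90 − 1 | 11.1% |
| 15% | 1/0.85 − 1 | 17.6% |
| 20% | 1/0.80 − 1 | 25.0% |

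**Step 2. Would such a rise reach significance alone?** This uses a paired t-test on the log scale, two-sided 0.05, with a mean log change of −ln(1 − f) and no true response. The table gives the chance of p < 0.05 with all 40 participants.

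| f | SD 0.2 | SD 0.3 | SD 0.5 |
|---|---|---|---|
| 5% | 35% | 18% | 10% |
| 10% | 90% | 58% | 26% |
| 15% | over 99% | 92% | 52% |

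With 32 participants (40 × 0.8), the f = 10% row becomes 82%, 49% and 21%.

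**Step 3. Which markers are exposed?** If the true fold change is T, the observed fold change is T/(1 − f). The share of the observed log rise that is due to volume is −ln(1 − f) / ln(T/(1 − f)). For T = 1.2 and f = 10%, this is 0.105/0.288 = 37%.

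| True fold change | f = 10% | f = 15% |
|---|---|---|
| 1.0 (none) | 100% | 100% |
| 1.2 | 37% | 47% |
| 2 | 13% | 19% |
| 8 | 5% | 7% |

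The problem is confined to markers with small true changes.

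**Step 4. Comparison between arms or tests.** With losses f1 and f2, the ratio of response ratios is (1 − f2)/(1 − f1).

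- 10% and 10%: 0.90/0.90 = 1, so nothing remains.
- 12% and 10%: 0.90/0.88 = 1.023, so 2.3% remains.
- 15% and 10%: 0.90/0.85 = 1.059, so 5.9% remains.

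**Step 5. Number of blood counts for the fix.** There are two samples around each of two bouts, one during the maximal test (the number is not stated; one is assumed) and one at 5 min, which makes six. If the sample after the submaximal bout also serves as the one before the maximal bout, there are five. Over two tests and 40 participants this gives 5 × 2 × 40 = 400 to 6 × 2 × 40 = 480.

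**The case against.** The strongest reply is that the Protocol does what it says. It names plasma concentrations as the outcome and measures them. It never names release as the target, so its sections do not contradict one another. That is right, and the uncorrected concentration is worth reporting. It does not settle the matter, because the background section intends to read the changes as inflammatory responses, and a concentration alone does not support that reading when the change is small.

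A second reply is that the Protocol is silent on correction, and that an SAP or laboratory procedure may deal with it. A reader might infer that the plan chose raw values. The text does not say so, and the point is not put that way. What stands is that no listed measurement would allow a correction.

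A third reply is that the size is wholly assumed. This is true of the 5% to 20% range, and the rejection rates in Step 2 rest on a further assumed SD. Nothing in the Protocol supports the upper end for a treadmill walking test in these patients.

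A fourth reply concerns training. A reader might infer that the artefact would pass as a training effect, because fitter participants may reach a higher load at the second test. The documents do not establish this. Equal shifts cancel, a residual needs an assumed difference in loss between arms, and the fixed-load bout has its load set by design. This part is a possibility only.

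**Conclusion.** The point holds in a limited form. As planned, a small within-person rise in IL-6, IL-18 or TNF-alpha around the maximal bout cannot be attributed to an inflammatory response, because nothing is measured that would separate it from a fall in plasma volume. Under an assumed loss of 5% to 20%, the apparent rise is 5.3% to 25.0%. This rests on the markers staying in the plasma and on a loss for which the Protocol gives no figure.

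Two wider readings are not supported. Lactate should not be grouped with the cytokines: it is not an inflammatory marker, and a several-fold rise would be little affected (5% to 7% of the log rise if the increase is eight-fold). Nor does the point touch the randomised ASDAS comparison or the sample size. It is a worthwhile improvement to a secondary aim and does not threaten the trial's main result.

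**What to change.** Add haemoglobin and haematocrit to every acute-exercise blood sample, at both tests. Calculate plasma volume relative to the first pre-exercise sample, which is the one before the submaximal bout:

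volume ratio = (Hb first / Hb later) × (1 − Hct later) / (1 − Hct first)

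Multiply each later cytokine concentration by this ratio. Report IL-6, IL-18 and TNF-alpha both uncorrected and corrected, and claim an acute inflammatory response only if it persists after correction. Lactate can stay uncorrected.

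The cost is about five or six counts per test, or roughly 400 to 480 in all. No extra visit is needed. A small extra tube per draw may be, since the Protocol does not give tube types or volumes. Corrected values will be slightly noisier, because they carry the measurement error of two further assays. The change has to be made before sampling starts.

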### Exercise intervention

The exercise intervention will be carried out at a fitness center with supervision from a physiotherapist.

A cardiorespiratory and muscle strengthening exercise program following the American College of Sports Medicine (ACSM) recommendations for maintenance and improvement of physical fitness. Cardiorespiratory fitness: two interval sessions (4 x 4 min), one continuous moderate exercise session (40 min) on a treadmill. The muscle strength exercises will consist of: 15-20 repetitions, large muscle groups as thighs, back and abdomen.

Dose: 12 weeks. Three times a week, 60 minutes.

Participants in the control group will be asked to continue their usual physical activity habits and will neither be encouraged nor discouraged from exercising. After the intervention period the control group will be offered an individually adapted exercise program and three exercise sessions with supervision from a physiotherapist.

